## Abstract

**Background:**

Approximately 10% of the individuals experiencing the death of a loved one develop prolonged grief disorder (PGD) after bereavement. Family members of haematological cancer patients might be particularly burdened since their loss experience is preceded by a very strenuous time of disease and aggressive treatment. However, support needs of relatives of cancer patients often remain unmet, also after the death of the patient. Therapeutic possibilities are enhanced by providing easily available and accessible Internet-based therapies. This study will adapt and evaluate an Internet-based grief therapy for bereaved individuals after the loss of a significant other due to haematological cancer.

**Methods:**

The efficacy of the Internet-based grief therapy is evaluated in a randomized controlled trial with a wait-list control group. Inclusion criteria are bereavement due to hematological cancer and meeting the diagnostic criteria for PGD. Exclusion criteria are severe depression, suicidality, dissociative tendency, psychosis, posttraumatic stress disorder, substance use disorder, and current psychotherapeutic or psychopharmacological treatment. The main outcome is PGD severity. Secondary outcomes are depression, anxiety, somatization, posttraumatic stress, quality of life, sleep quality, and posttraumatic growth. Data is collected pre- and posttreatment. Follow-up assessments will be conducted 3, 6, and 12 months after completion of the intervention. The Internet-based grief therapy is assumed to have at least moderate effects regarding PGD and other bereavement-related mental health outcomes. Predictors and moderators of the treatment outcome and PGD will be determined.

**Discussion:**

Individuals bereaved due to haematological cancer are at high risk for psychological distress. Tailored treatment for this particularly burdened target group is missing. Our study results will contribute to a closing of this healthcare gap.

**Trial registration:**

German Clinical Trial Register UTN: U1111–1186-6255. Registered 1 December 2016.

## Background

Grieving is an emotional reaction to the loss of a loved one and refers to the transition between the loss experience and the adaptation to it [1] whereby intense feelings of mourning and yearning are considered normal and typically decrease over time [2]. According to Stroebe and Schut [3] the process of coping with bereavement is characterized by an oscillation between loss-oriented and restoration-oriented stressors. During this process the bereaved person alternates between confrontation with and avoidance of the different tasks of grieving which results in adjustment to bereavement.

However, some individuals develop a persistent grief reaction which is described as persistent complex bereavement disorder by the DSM-5 in the chapter of diagnoses that require further research [4]. In the ICD-11 this syndrome of persistent grief will probably be included as Prolonged Grief Disorder (PGD) [5]. DSM-5 and ICD-11 criteria for grief disorders describe the same diagnostic entity, differing merely semantically [6]. PGD is characterized by intense symptoms of grief enduring for more than 6 months post-loss, separation distress, intrusive thoughts, and feelings of emptiness or meaninglessness [7]. A recent meta-analysis revealed a prevalence of about 10% for PGD among bereaved adults [8]. The loss of a loved one can not only trigger PGD but also depression, anxiety, or posttraumatic stress disorder (PTSD) [9]. Persons suffering from chronic grief experience elevated levels of depression and mortality [10].

A loss due to cancer was shown to be a risk factor for PGD [11, 12] and depression [12] and to be as distressing as an unexpected natural loss (e.g., due to cardiac arrest, accident) [12]. Cancer ranks among the leading causes of morbidity and mortality worldwide [13]. In 2013 haematological cancer was the third most common cancer-related cause of death in Germany with 18,831 people who died due to this disease [14].

Cancer is a significant psychological burden for patients and for their loved ones. During the time of illness significant others of cancer patients show high distress with prevalence rates of 20 to 46% for depression and anxiety [15, 16], and lower health-related quality of life than the general population, especially if cancer is advancing [17]. Levels of distress, depression, and anxiety of family members were shown to be similar or even higher compared to cancer patients [15, 18–20]. Declined functional status and increased physical symptoms as well as higher psychological distress in cancer patients are associated with higher caregiver distress [18, 21, 22]. Especially haematological cancer patients are burdened by long and aggressive cancer treatments [23, 24] and show high distress [19, 20, 25, 26], as do their family members [19, 20, 26, 27]. These findings suggest a particularly high risk for adverse psychological outcomes in family members of haematological cancer patients. Yet, relatives of haematological cancer patients report more unmet supportive care needs than patients [20].

In the case of bereavement caregivers of cancer patients show a deterioration in mental health [28–30]. Impaired mental health during the time of the cancer experience predicted worse mental health after bereavement [31] and PGD [32]. Caserta and colleagues argue that a burdensome time of illness may deplete resources and impede bereavement adjustment [12].

Tough relatives of haematological cancer patients may be assumed to be at heightened risk for adverse outcomes after bereavement, there is a lack of studies focusing on bereavement adjustment among relatives of patients with haematological cancer. To our knowledge, only one study examined psychological well-being after bereavement due to haematological cancer and found lower psychological well-being in bereaved parents of children who underwent haematopoietic stem cell transplantation compared to other cancer-bereaved parents [33].

These results underline the need for support for bereaved relatives of cancer patients. Easily available and accessible support can be provided by Internet-based programs [34, 35]. Compared to face-to-face therapy Internet-based interventions facilitate more flexibility and anonymity as well as faster attainability [36, 37]. Internet-based interventions and face-to-face therapy show comparable positive effects, e.g., for depression [38]. Participants in Internet-based treatments reported a positive working alliance [39–42]. Despite the advantages of Internet-based programs Northouse et al. [43] found no study with an Internet-based intervention in their review of psychosocial interventions for caregivers of cancer patients. Therefore, our Internet-based grief therapy constitutes an important innovation, closing a research and supply gap.

In our study we use an Internet-based cognitive-behavioural grief therapy originally developed as “Interapy” by Lange and colleagues for the treatment of posttraumatic stress [35]. For the treatment of PGD cognitive-behavioural therapy proved efficacious, particularly exposure therapy [44, 45]. Interapy was adapted for PGD [46] and its efficacy was shown for various groups of bereaved individuals showing medium to large treatment effects [46, 47].

The main goal of our study is the adaptation and evaluation of the Internet-based cognitive-behavioural grief therapy for bereaved persons after the loss of a significant other due to haematological cancer, targeting primarily the reduction of PGD severity. The results of our study will provide information about the efficacy of Internet-based therapy for people who experienced a loss which is usually expected but preceded by a very burdensome time of disease and aggressive treatment.

## Methods

The guided text-based intervention for people who suffer from PGD after bereavement due to haematological cancer is currently evaluated in a randomized waitlist-controlled trial. Questionnaires are administered at screening for eligibility (T-1), at baseline (T0), during the intervention (monitoring), at post-treatment (T1) and at three follow-up points (T2–4; 3, 6, and 12 months after intervention completion). Severity of PGD symptoms as measured with the Inventory of Complicated Grief (ICG) [48] is the main outcome. All questionnaires and the intervention are administered via a secure website and data is stored on secure storage devices. The procedure is described in detail below.

### Procedure

#### Recruitment practices

Short information about the study and a link to the study website is sent to a multitude of stakeholders, including support groups, charities, insurance companies, clinics and medical practices, owners or contact persons of relevant websites, online communities, and blogs in Germany. Flyers are sent via mail by request and distributed in departments of the University Medical Centre Leipzig, e.g., Psychosomatic Medicine, Medical Psychology and Medical Sociology, and Haematology and Medical Oncology.

The study website provides thorough information about the study and the Internet-based grief therapy. Interested persons can apply by submitting a screening questionnaire which determines whether they fulfil eligibility criteria. Contact information of the research team is provided to be addressed in case of questions and remarks.

#### Participant timeline

The procedure from screening to follow-up assessments is depicted in Fig. 1.

**Fig. 1 Fig1:**
[figure not shown]
Participant timeline

*T-1, screening:* Participants apply for the study via an openly accessible online questionnaire. Participants who may fulfil the eligibility criteria as described below will be contacted for a telephone screening, which includes the Prolonged Grief Interview [7, 49] and in case of eligibility concerns queries regarding participant’s answers in the online questionnaire. Participants who do not fulfil the eligibility criteria but show signs of suicidal ideation will also be called to ensure their safety and provide support in finding immediate help if necessary. Participants who are excluded from the study after the screening process will receive information about the reasons via e-mail and be offered help in finding an alternative treatment.

*Informed consent:* Participants meeting the eligibility criteria will be sent thorough information on the study and asked to send back a consent form, which also includes contact information of the participant’s general practitioner, who will be contacted in case of endangerment to self or others. Participants are informed about this requirement. Questions can be addressed to the research team at any time.

*T0, baseline:* After written informed consent, participants receive a personal link to the baseline questionnaire. Upon submission of this questionnaire participants are randomized as described below.

*Treatment:* The intervention group (IG) receives the intervention as described below. Those assigned to the waitlist-control group (WCG) will wait for five weeks before completing the first post-treatment assessment (T1.0). Subsequently, the same intervention as described above will be provided and an identical post-treatment assessment will be administered (T1.1) after the intervention. Participants in the WCG will be informed about this procedure immediately after randomization. For the sake of clarity the following nomenclature will be used subsequently: “treatment” describes the study phase between baseline and post-measurement and includes IG and WCG; “intervention” describes the Internet-based therapy that is conducted during treatment for IG and after the first post-treatment assessment for WCG.

*T1, post-treatment:* After completion of treatment, participants receive a link to the post-treatment questionnaire. The WCG receives an identical questionnaire again after completing the intervention.

*T2–4, follow-up:* 3, 6, and 12 months after cessation of the intervention, links to online follow-up questionnaires are sent to participants of both groups. All follow-up questionnaires are identical.

#### Randomization

Randomization takes place after the baseline assessment. Participants are randomized into one of two groups: IG or WCG. A permutated block randomization with a block size of four and equal probabilities to be sampled into either group is carried out with pseudo-seeds, using MersenneTwister. The used software was “Randomization in Treatment Arms” (RITA). Neither participants, nor the research team were blind to group allocation. Yet, this is not expected to lead to biased results, since all assessments after randomization are carried out anonymously and automated via online questionnaires.

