Self-esteem	Rosenberg self-esteem scale [94, 95]	10	not at all true-completely true (0–3)	present	*α*=.72–.85 [95]		x		x
Self-efficacy	Skala zur Allgemeinen Selbstwirksamkeitserwartung (Self-Efficacy Scale, SWE) [96] (originally German)	10	not at all true-completely true (1–4)	present	*α*=.80–.90 [96]		x		x
Coping strategies	Brief COPE [97, 98]	28	not at all-a lot (1–4)	lifetime	*α*=.61–.81 [98]		x		x
Stigma	Grief Experience Questionnaire (GEQ), subscale Stigmatization [60], own translation	10	never-almost always (1–5)	since loss	*α*=.86 (English version) [60]		x		x
Working alliance	Working Alliance Inventory Short Form (WAI-S) [54, 99] (only Monitoring and T1)	12	never-always (1–7)	intervention	*α*=.81–.91 [99]			x	x
Mood	Self-Assessment Manikin (SAM) [52]	3	(1–9)	present	–			x	

^a^Where a cut-off value is provided, it is used at T-1 to determine whether a participant fulfils eligibility criteria

Abbreviations: *α*=Chronbach’s alpha (internal consistency); r_tt_ = test-retest reliability

Published German translations of measurement tools are used where available. For all other measurement tools [57–60], own translations were achieved as follows: the first authors translated the measurement tools from English to German. A native English speaker retranslated the result, which was then checked for accordance with the original tool. Any inconsistencies and challenges in translating, e.g., idioms, were discussed thoroughly within the research team.

In addition to the variables listed in Table 2, sociodemographic variables, current medical problems, drug and alcohol consumption, history of previous losses, traumatic experiences, and of psychological problems, and help-seeking behaviour are assessed at baseline (T0).

All measures except the Prolonged Grief Interview [49, 61] are assessed by online self-assessment questionnaires which minimizes potential assessment bias.

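### A single published block size of four, with a research team that sees allocations, leaves up to one third of allocations predictable at the point of randomisation

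*Protocol article*

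**What the plan says.** The Randomization section of the Protocol article fixes the scheme as "A permutated block randomization with a block size of four and equal probabilities to be sampled into either group". It names no second block size and no stratification factor. It continues: "Neither participants, nor the research team were blind to group allocation". It then says that this should not bias the results, "since all assessments after randomization are carried out anonymously and automated via online questionnaires".

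The Participant timeline section gives the order of entry. Applicants complete an open online questionnaire. Those who may qualify "will be contacted for a telephone screening, which includes the Prolonged Grief Interview", together with queries about their answers where eligibility is in doubt. The Measurements section confirms that this interview is the one exception to online self-report: "All measures except the Prolonged Grief Interview" are collected by online questionnaire. Study information and a consent form follow. Then: "After written informed consent, participants receive a personal link to the baseline questionnaire". Finally: "Upon submission of this questionnaire participants are randomized as described below". These sentences name no role for the person who telephones, sends the documents or releases the link.

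The target is 128 participants, 64 per group (Sample size and power calculation). The opening of the Methods describes the evaluation as under way, so the block size was published while the trial was running.

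**The concern.** With one known block size and visible past allocations, anyone keeping count can tell what some of the next allocations will be. The fourth place in a block is always determined, and the third is determined whenever the first two match. If such a person can also influence who enters next, or when, applicants can be steered consciously or not, for example by holding one back until an intervention slot comes up. The groups would then differ by selection. Adjustment for measured baseline variables cannot fully repair that, and the primary outcome is a self-report scale completed by unblinded participants.

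The article's reassurance does not meet this risk. Automated questionnaires after randomisation limit the influence of an assessor on the outcome. They do nothing about who is placed in which group beforehand.

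**Working it through.** **Inputs.** Block size 4, allocation 1:1 and an unblinded team (Randomization section); N = 128 (Sample size and power calculation). Assumptions: one sequence without strata, since none are named; and an observer who knows where each block begins.

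**The plan's own figure.** The article gives no predictability figure, only N. With d = 0.5 taken as moderate and a two-sided alpha of 0.05 (the article states neither the value of d nor the sidedness), a two-sample t-test at 80% power needs 63.77, hence 64 per group. This reproduces the stated 128.

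**Certain knowledge, all earlier allocations seen.** A block has six equally likely sequences: AABB, ABAB, ABBA, BBAA, BABA, BAAB.
- Places 1 and 2: never certain, so 0 and 0.
- Place 3: certain if the first two match, 2/6 = 1/3.
- Place 4: always certain, 1.

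Share = (0 + 0 + 1/3 + 1)/4 = 1/3. With 128/4 = 32 blocks, this is 32 × (1 + 1/3) = 42.7 allocations.

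**Best guess, all earlier allocations seen.** Success by place is 1/2, 2/3, 2/3 and 1. The third is 1/3 × 1 + 2/3 × 1/2 = 2/3. Mean = (17/6)/4 = 17/24 = 70.8%, against 50% under simple randomisation.

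**Unseen allocations in between.** Eligibility is settled well before randomisation, so others may be randomised in the meantime.
- One in between: place 4 is certain only if places 1 and 2 matched, so the share is (1/3)/4 = 1/12 = 8.3%, or 10.7 of 128. Best guess = (1/2 + 1/2 + 2/3 + 2/3)/4 = 7/12 = 58.3%.
- Two in between: no place is certain, so 0%. Best guess = (1/2 + 1/2 + 1/2 + 2/3)/4 = 13/24 = 54.2%.

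**Other schemes, all earlier allocations seen.** Fixed sizes are enumerated exactly. Mixed sizes come from 400 simulated trials of 128, with sizes drawn with equal probability and an observer who knows the set of sizes but not the size of the current block.

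| Scheme | Certain | Best guess |
|---|---|---|
| Fixed 4 | 33.3% | 70.8% |
| Fixed 6 | 25.0% | 68.3% |
| Fixed 8 | 20.0% | 66.6% |
| Mixed 4/6 | 5.4% | 69.2% |
| Mixed 4/6/8 | 2.5% | 68.2% |

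**The case against.** The strongest case against the point is that the article shows no route by which predictability would be used. A reader might infer that the same unblinded team decides eligibility and sends the baseline link. That is a natural reading, since no separate screener is named, but the text is in the passive throughout and does not say so. Nor does it say who operates the randomisation software or sees its list, and a condensed article may leave that to the full protocol.

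Discretion is also limited. The footnote to Table 2 says that the listed cut-offs decide eligibility at screening, and apart from the interview these rest on online self-report. Human judgement remains in the interview and in the queries about doubtful answers. Consent and baseline submission come after eligibility, and it is the participant's own submission that triggers randomisation. The control group also receives the intervention after a five-week wait, which weakens the motive to steer.

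Finally, the contrast of 71% with 50% mostly reflects permuted blocks under open allocation in general, because mixed sizes barely change it.

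All of this stands, and it limits the size of the point. It does not remove it: the single block size and the open allocation are both stated, and the article's argument against bias leaves selection before allocation unaddressed.

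**Conclusion.** The point holds as a design weakness with a range, not as evidence of bias. At the moment of randomisation, and with every earlier allocation known, up to one third of allocations (at most about 43 of 128) are certain. The share is 8.3% if one unseen allocation intervenes and zero if two do. Where the trial falls in this range depends on how densely applicants enter and on whether anyone controls the timing of the baseline link. The article gives neither.

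A reader might infer that a third of allocations were knowable when eligibility was decided, or that entry was in fact steered. The document supports neither: the one-third figure applies at randomisation and not at screening, and the roles are unstated. The absence of a described concealment procedure is not counted here. What can be said firmly is that the fixed block adds avoidable predictability, and that the reassurance in the Randomization section reaches further than its reason allows.

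**What to change.** For any remaining recruits, replace the fixed block with sizes varying at random, for example 4, 6 and 8, and do not disclose the sequence of sizes to anyone who screens applicants or sends the baseline link. Start the new scheme at the end of a completed block and record the date. Certain predictions fall from 33.3% to about 2.5%, roughly 3 of 128 (0.025 × 128 = 3.2) if applied throughout. Best-guess success falls only to about 68%, so the gain lies in removing certainty, not in making guesses useless.

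Reword the no-bias sentence so that it claims only that automated questionnaires limit bias in outcome assessment. If recruitment has closed, this rewording is the part that can still be done.

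The cost is a software setting and a sentence. The downside is a possible final imbalance, at most half the largest block, so 4 participants with blocks up to 8. A split of 66 to 62 is equivalent to 2 × 66 × 62/128 = 63.9 per group instead of 64, which is negligible.

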### Intervention

Participants will receive therapist-assisted Internet-based grief therapy which applies the paradigm of structured writing. All therapeutic content, such as general information and writing instructions, is presented through a secure website (“Beranet”). Communication with the therapist is also conducted via an e-mail function of this website.

The Internet-based cognitive-behavioural grief therapy aims at working through the grief as well as coping with the new situation [46]. It is derived from a rationale developed by Lange et al. for individuals suffering from posttraumatic stress [35] which was adapted for PGD by Wagner et al. [46, 50, 51]. It is structured as a sequence of ten writing tasks in three phases: (1) self-confrontation, (2) cognitive restructuring, and (3) social sharing. The first phase focuses on loss-oriented coping, whereas phases two and three refer to restoration and integration of the loss experience [46].

Participants are instructed to plan out two writing tasks per week in advance, each lasting 45 min. They receive access to each writing task upon having completed the previous task. Once a week participants receive thorough feedback for their writing tasks from their therapist. All therapists are psychologists who were trained in the application of the intervention manual and receive supervision. Instructions for the writing tasks are mainly standardized and therapist instructions for individualized feedback are highly structured. Other than sending new writing tasks and feedback, therapists engage in further communication when directly contacted by the participant or when participants express critical experiences such as high distress or suicidal thoughts. In this case therapists address existing issues via mail or, if necessary, telephone. In case of endangerment of self or others, the participant’s general practitioner will be contacted to initiate immediate care for the participant.

Prior to the first phase, participants receive general information on the treatment, psychoeducation on the phases, and instructions on how to use the treatment platform. An overview of the Internet-based grief therapy and monitoring can be found in Table 1.

**Table 1 Tab1:** Intervention overview

Week	Phase	Procedure				
		Pre-Task- Monitoring		Task	Post-Task Monitoring	
1	Phase 1: Confrontation	SAM		Task 1	SAM	
		SAM	PHQ-9	Task 2	SAM	
		therapist feedback				
2		SAM		Task 3	SAM	
		SAM	PHQ-9	Task 4	SAM	WAI-S

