### Measurements

The ICG [48] is used in its German version [55] to measure the primary outcome severity of PGD symptoms. It measures severity of PGD by assessing symptoms related to grief like yearning, intrusive thoughts, or resentment regarding the loss in 19 items which are rated by participants on a five-point Likert scale (never-always, 0–4) with regard to the last month. Three additional items were administered that are not included in the sum score but shall serve future comparability in the case of inclusion of PGD in ICD-11 as suggested by Maercker et al. [5]. They address feelings of guilt, difficulty accessing positive memories and anhedonia in questions adapted from Xiu et al. [56] as follows “I feel guilty about mistakes I made with regard to his/her death”, “It is really difficult for me to remember in detail happy moments with or images of him/her from the times before he/she died,” and “I no longer feel able to experience happiness, contentment, or joy since the loss of this person.”

Secondary outcomes, screening variables, moderators and mediators as well as used measures are summarized in Table 2.

**Table 2 Tab2:** Measurement tools

Construct	Instrument (abbreviation) [original and German source], additional information		Rating		Reliability	T-1	T0	Monitoring	T1-T4
		Item No.	Likert scale wording (scores)	Time frame					
Prolonged grief	Inventory of Complicated Grief (ICG) [48, 55], Cut-off^a^: ≥25 (sum score) [48]	19	never-always (0–4)	last month	*α*=.87, r_tt_ = .69 [55]	x	x		x
	Additional items [56], German version received from [name]	3	never-always (0–4)		–	x	x		x
	Prolonged Grief-13 – Interview version (IKT), [49, 61]	13	various formats (mostly 5-pointlLikert scales)	last month	–	x			
Depression	Patient Health Questionnaire (PHQ-9) [53, 62], Cut-off: ≥20 (sum, for severe depression) [63]	9	not at all-nearly every day (0–3)	last 2 weeks	*α*=.88 [64]	x	x	x	x
Posttraumatic stress	Impact of Event Scale-Revised (IES-R) [65, 66], Cut-off: > 0 (regression formula) [66], Screening: due to an event other than the loss, Baseline and post-assessments: due to loss	22	not at all-often (0,1,3,5)	last week	*α*=.71–.90, r_tt_ = .66–.80 [66]	x	x		x
Suicidal Ideation	Scale for Suicide Ideation (BSS or BSIS) [67, 68]	21	various formats (3 nuances each)	last week	*α*=.84–.89 [69]	x			

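### The article infers no bias from automated questionnaires, but unblinded participants rate the primary outcome themselves, so expectancy-driven reporting is not excluded

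*Protocol article*

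**What the plan says.** The Randomization section of the protocol article is open about blinding: "Neither participants, nor the research team were blind to group allocation". It then draws a conclusion about bias: "Yet, this is not expected to lead to biased results, since all assessments after randomization are carried out anonymously and automated via online questionnaires".

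Three other places bear on that conclusion.

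- **Measurements.** The primary outcome, the ICG, consists of "19 items which are rated by participants on a five-point Likert scale". All instruments other than the Prolonged Grief Interview are described as "online self-assessment questionnaires which minimizes potential assessment bias". Table 2 places that interview at screening only.
- **Participant timeline, Treatment.** Controls wait five weeks, complete the first post-treatment assessment (T1.0), and then receive the same intervention. "Participants in the WCG will be informed about this procedure immediately after randomization".
- **Intervention.** The therapy is therapist-assisted: "Once a week participants receive thorough feedback for their writing tasks from their therapist".

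The Statistical analysis section tests the treatment effect by comparing the change from baseline to post-treatment between the two groups.

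**The concern.** The reason offered for expecting no bias concerns how the answers are collected. The risk in an unblinded trial with self-reported outcomes lies mainly with the person who answers. Here that person knows whether they have just finished a course of therapy or are still waiting for one. What they expect from treatment, or how they react to having to wait, can affect how they score their own grief, whether or not a member of staff sees the form.

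The comparison affected is the one that matters most. Once T1.0 is complete the controls receive the intervention, so intervention-group T1 against waitlist T1.0 is the only contrast with an untreated arm. If the assurance in the Randomization section is carried into the reading of that contrast, a positive result will be taken to be free of a source of bias that the design does not control.

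**Working it through.** **Step 1. Which sources of bias does the stated reason cover?**

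| Possible source | Covered by automated, anonymous online forms? | Basis in the article |
|---|---|---|
| Interviewer or assessor influence after randomisation | Yes | All post-randomisation measures are online self-report |
| Answering to please staff | Perhaps in part, through anonymity | Randomization; the mechanism is not described |
| Expectancy or reactive reporting by a participant who knows the arm | No | Participants are unblinded and rate the ICG themselves; controls are told of the wait at once |

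The claim in Randomization concerns results in general, while its reason reaches only the first row and possibly part of the second. The article describes no post-randomisation rating by anyone other than the participant. The baseline form goes out by personal link, and a repeated-measures analysis needs each person's two scores paired. Anonymity must therefore mean coded, linkable data. That may still shield answers from therapists, but it does not blind the rater.

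**Step 2. The plan's own figure.** Taking the unquantified moderate effect as d = 0.5 (an assumption), two-sided alpha 0.05 and power 80%:

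- Normal approximation: n per group = 2(1.960 + 0.842)² / 0.5² = 62.8, so 63.
- Two-sample t-test (noncentral t): 63.77, so 64 per group and 128 in total, with power 80.1%.

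The stated sample size reproduces and is not in dispute.

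**Step 3. Illustration of what an uncontrolled shift could do.** No size is given in the documents, so a range is assumed. Let the therapy effect be zero and let knowledge of allocation shift mean self-ratings between groups by b SD. With n = 64 per group, the two-sample t statistic has noncentrality b × √(64/2) = 5.657b on 126 degrees of freedom.

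| Assumed b (SD) | Noncentrality | Probability of p < 0.05, two-sided |
|---|---|---|
| 0 | 0 | 5.0% |
| 0.1 | 0.566 | 8.7% |
| 0.2 | 1.131 | 20.2% |
| 0.3 | 1.697 | 39.1% |

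**Step 4. Link to the planned test.** The group-by-time term of a 2 × 2 repeated-measures ANOVA is equivalent to a t-test on change scores. With equal SDs and baseline to post-treatment correlation ρ, the standardised shift is b / √(2(1 − ρ)). At ρ = 0.5 the divisor is √1 = 1, so the table applies unchanged. A lower ρ gives smaller probabilities and a higher ρ larger ones. The article does not state ρ for this trial, so the table is a guide to order of magnitude and nothing more. A shift against the intervention would hide a real effect instead of creating a false one.

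**The case against.** Participants in a psychotherapy trial with a waiting list cannot readily be blinded, and the comparator is declared openly in the Abstract and Methods. That stands. The point is not an objection to the open-label waitlist design, and it asks for no change to it.

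Several stronger readings may tempt a reader, and the documents do not support them.

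- *Therapist attention is a bias.* It is not. The intervention is defined as guided and therapist-assisted, so weekly feedback is part of what is being evaluated. Only expectancy-driven or reactive reporting remains as a possible bias.
- *The article claims efficacy net of attention and expectancy, or commits the authors to calling the result unbiased.* No section does so. The aim and Discussion speak of efficacy without that qualification, and Randomization states an expectation, not a reporting rule.
- *Anonymity is worthless here.* That is not shown. It may reduce some socially desirable answering.
- *The Measurements sentence is false as well.* It speaks of minimising, not excluding, and contrasts questionnaires with the one interview. It reads most naturally as a remark about interviewer bias.
- *The result will be biased in favour of the intervention.* No passage gives a direction or size, and the shifts in the table are assumptions that would suit any unblinded trial with 64 per group.

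None of this repairs the inference in Randomization. Unblinding that cannot be avoided is a reason to acknowledge participant-level reporting bias, not to say that none is expected. Nor is this a matter of condensed text, since the fault lies in a sentence that the article does contain.

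**Conclusion.** The sentence in Randomization is wrong as written: it attributes to the design a protection that the design does not have. This follows from the article's own statements that participants are unblinded, that they rate the primary outcome, and that controls are told of their wait immediately. It needs no outside figure.

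What is established is the absence of the claimed protection. Neither the presence of bias nor its size or direction is established. The illustrative 9%, 20% and 39% rest on assumed shifts of 0.1, 0.2 and 0.3 SD, a zero therapy effect, 64 analysed per group, and either a simple t-test or a baseline to post-treatment correlation of 0.5. They show only that a modest shift would not be negligible at this sample size.

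The consequence is confined to interpretation. Sample size, data collection and analysis are unaffected.

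**What to change.** Three changes of wording.

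1. In Randomization, replace the statement that no bias is expected with one saying that automated online assessment limits interviewer bias only, and that participants are unblinded raters of the primary outcome.
2. In Measurements, make clear that the assessment bias referred to is interviewer bias.
3. When reporting the baseline to post-treatment contrast, limit the conclusion to guided therapy, including therapist contact, versus an announced five-week wait, and state that participant expectancy was not controlled.

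The cost is a slightly less favourable account of what a positive result would show. Nothing changes in design, conduct or analysis.
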